## Abstract

**Background:**

Hospitalized older adults spend as much as 95% of their time in bed, which can result in adverse events and delay recovery while increasing costs. Observational studies have shown that general mobility interventions (e.g., ambulation) can mitigate adverse events and improve patients’ functional status. Mobility technicians (MTs) may address the need for patients to engage in mobility interventions without overburdening nurses. There is no data, however, on the effect of MT-assisted ambulation on adverse events or functional status, or on the cost tradeoffs if a MT were employed. The AMBULATE study aims to determine whether MT-assisted ambulation improves mobility status and decreases adverse events for older medical inpatients. It will also include analyses to identify the patients that benefit most from MT-assisted mobility and assess the cost-effectiveness of employing a MT.

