## Objectives {7}

AMBULATE has three primary aims: first, to determine whether an ambulation program delivered by a MT improves patients’ mobility status at hospital discharge. As related objectives, we will examine if the intervention decreases hospital-related complications, including falls, venous thromboembolism, pressure ulcers, and hospital-acquired pneumonia; if it impacts discharge disposition (i.e., home vs. post-acute care facility); and if mobility improvement is sustained after hospital discharge. Second, we will use predictive modeling to identify which patients are more likely to benefit from this intervention. Third, we will assess the impact of the intervention on overall costs associated with the episode of care, including inpatient costs and medical costs following discharge.

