### Sample size {14}

A sample size of 3000 has >99% power to detect a difference in SPPB change as small as 0.54 points (the MCID) between the two groups at a two-sided alpha of 0.05, assuming a common SD of 2.7 for the SPPB change, 20% non-compliance, 10% dropouts, and an interim analysis. The estimates for MCID and SD are based on observation of older acute care medical patients [43, 44]. Using these same assumptions, the power is still 92% for detecting a smaller difference of 0.35. Therefore, we expect ample statistical power for analyzing the primary outcome. The main reason for selecting this sample size is to ensure that the analyses of important secondary outcomes are not underpowered. The most important of these is discharge disposition, because even a small absolute difference in the number of patients discharged to home, as opposed to a skilled nursing facility, is clinically important. We will be able to detect a 7% difference in discharge to home vs. SNF with 98% power.

For other binary secondary outcomes (a combination of venous thromboembolism, pneumonia and falls, 30-day mortality, or 30-day readmission), the study will have 85% power to detect a 33% reduction assuming an 8% rate in the control group. Because these outcomes are not contingent on patient cooperation, we anticipate no dropouts. For secondary continuous outcomes such as length of stay, assuming 20% non-compliance rate, the power to detect a 4-h difference (0.167 days) is 95%.

Regarding the cost analysis, there is no accepted way of doing a power calculation. However, we tried adding $300 (an approximation of the cost of the intervention) to the costs of each of 1500 patients drawn randomly from a sample of 3000 Cleveland Clinic medical inpatients over the age of 65 with an AM-PAC 6-Clicks score between 16 and 20. We then performed a *t*-test on the log-transformed costs, as described in the economic analysis section, and we were able to detect the increase with a p-value of 0.03, indicating that should the intervention increase costs by an amount equal to the cost of the intervention, we should be able to identify it. Similarly, if the intervention decreases total costs by $300 or more (not including the costs of the intervention), we should have sufficient power to detect it.

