### Methods for additional analyses (e.g., subgroup analyses) {20b}

We will conduct three sensitivity analyses to account for (1) missing outcomes data, (2) treatment heterogeneity by site, and (3) the dose-response curve in the intervention group.

To identify the patients most likely to benefit from ambulating with a MT, we will build models separately for each treatment arm to predict the outcome of at least 1-point increase in the SPPB (i.e., beyond the minimal clinically important difference). Using the predicted probabilities resulting from these models, we will develop a Classification and Regression Tree (CART) that should identify subsets of patients likely to benefit, not benefit, or be harmed by the treatment. For example, the analysis might show that female patients aged >75 years who have an initial 6-Clicks score between 16 and 18 have an estimated treatment benefit of being 22% more likely to achieve the 1-point increase in SPPB. Essentially the tree will form risk groups of patients with shared characteristics that should receive a similar care recommendation.

We will estimate the total cost of the episode of care including the index admission (from hospital cost accounting systems) and all non-medication costs for the 30 days following enrollment (from Medicare claims) for all patients. For the intervention group, we will add the personnel costs for the MTs (hourly wages plus benefits). Since cost data are skewed, our cost estimates will be transformed and then compared between groups using the *t*-test.

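### The abstract promises cost-effectiveness, but the stated economic analysis is a log-scale t-test on cost alone, which neither relates cost to effect nor directly estimates the mean dollar difference

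*Protocol article*

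**What the plan says.** All references are to the protocol article.

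- **Abstract, Background.** The trial will "assess the cost-effectiveness of employing a MT". The same paragraph names the cost trade-offs of employing a mobility technician (MT) as a gap in the evidence.
- **Objectives {7}.** The economic aim is one of three primary aims and is stated in cost terms: "Third, we will assess the impact of the intervention on overall costs associated with the episode of care".
- **Methods for additional analyses {20b}.** This gives the method. "We will estimate the total cost of the episode of care including the index admission", to which non-medication costs for 30 days after enrollment are added from Medicare claims. "For the intervention group, we will add the personnel costs for the MTs (hourly wages plus benefits"). Then: "Since cost data are skewed, our cost estimates will be transformed and then compared between groups" by t-test.
- **Sample size {14}.** This section names the transformation. It describes "adding $300 (an approximation of the cost of the intervention") to half of a sample of 3000 past inpatients and running a t-"test on the log-transformed costs, as described in the economic analysis section".
- **Abstract Discussion and main Discussion.** These speak of implications for cost, and of intervention cost set against possible savings.

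**The concern.** Cost-effectiveness is a statement about two quantities: what was spent and what was gained. The stated analysis has only the first. It also handles that quantity on a scale that does not convert directly into dollars per patient.

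If the MT arm turned out cheaper and better, this would matter little, because a cost comparison beside the clinical results would settle the question. If the MT arm cost more and did better, the reader would need the size of the added cost, the size of the gain and their joint uncertainty. The stated plan supplies a test on log cost and separate tests on each outcome. The Discussion wants administrators to judge whether MT posts are feasible and useful. In that second case the plan as written does not give them the trade-off that the abstract announces.

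**Working it through.** **The plan's own figure.** The only number tied to the economic analysis is p = 0.03, from one exercise in Sample size {14}. It cannot be reproduced, because the mean and SD of cost, raw or log, are not given. Nothing below depends on it.

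**Step 1: the passages side by side.**

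| Place | Cost | Effect | Cost linked to effect |
|---|---|---|---|
| Abstract, Background | yes | yes (implied by cost-effectiveness) | promised |
| Objectives {7}, third aim | yes | no | no |
| Additional analyses {20b} | yes, t-test on transformed cost | no | no |
| Sample size {14}, cost paragraph | yes, t-test on log cost | no | no |
| Outcomes {12} | no | SPPB, disposition, complications, 30-day function | no |
| Discussion | cost against savings | no | no |

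The article names no cost-effectiveness ratio, net benefit, willingness-to-pay range or joint uncertainty. Only the first row promises the link, and no later row delivers it.

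**Step 2: what a log-scale t-test estimates.** Let log cost have mean μ and SD σ in an arm. The test compares μ between arms, that is, geometric means exp(μ). If cost is log-normal (an assumption), the arithmetic mean is exp(μ + σ²/2). With equal μ, the ratio of arithmetic means, intervention to control, is

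exp[(σ₁² − σ₀²)/2].

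The article gives no SDs. Assuming a control log-SD of σ₀ = 0.80:

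- σ₁ = 0.75: (0.5625 − 0.64)/2 = −0.03875, ratio 0.962, mean cost 3.8% lower
- σ₁ = 0.70: (0.49 − 0.64)/2 = −0.075, ratio 0.928, mean cost 7.2% lower
- σ₁ = 0.85: (0.7225 − 0.64)/2 = 0.04125, ratio 1.042, mean cost 4.2% higher

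In each case the quantity under test is exactly equal in the two arms although mean dollars differ. An intervention that mainly changed the expensive tail could produce this pattern.

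**Step 3: the same dollars count unequally on the log scale.** Adding $300 to an assumed $5,000 episode shifts log cost by ln(1 + 300/5000) = 0.0583. Adding it to an assumed $30,000 episode shifts log cost by ln(1 + 300/30000) = 0.00995. The first shift is about 5.9 times the second (0.0583/0.00995), although the hospital spends the same amount.

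**Step 4: what the promised question needs.** With ΔC the difference in arithmetic mean cost and ΔE the difference in effect, the usual measures are ΔC/ΔE, or the net benefit λΔE − ΔC at willingness to pay λ. The variance of the net benefit is

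λ²Var(ΔE) + Var(ΔC) − 2λCov(ΔE, ΔC).

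The log-scale test does not directly supply ΔC. Separate analyses of cost and outcome do not supply the covariance.

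**The case against.** The best defence is that one term in the abstract is loose and the rest agrees. The third aim, its method, the abstract's own Discussion and the main Discussion all speak of cost. Rewording the abstract would remove the mismatch. That stands as far as the mismatch goes. It does not deal with Steps 2 and 3: even a pure cost-impact aim is about dollars, and the stated test is not.

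A second defence is that the article is a condensation. Sample size {14} points to an economic analysis section, and the article has none with that title, only one paragraph under {20b}. A fuller protocol or analysis plan may contain a cost-effectiveness analysis. That limits the point to what is stated here. But the article is not silent: it fixes the aim and the method, both in cost-only terms.

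Third, {20b} says total cost will be estimated, so arm-level costs may well be reported beside the clinical results. That is fair, and it would be wrong to say that only a p-value will appear. Still, no estimate or interval is stated for the mean difference, and none for cost and effect jointly.

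Some stronger inferences are tempting but unsupported:

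- **That added cost with added benefit is the expected result.** Sample size {14} also considers a fall of $300 or more, and Trial design {8} reports shorter stays and more home discharges in the pilots.
- **That the $300 can be divided by the 7% discharge difference, or by the SPPB difference, to give a cost per unit of benefit.** These figures come from separate exercises. The $300 is the gross cost of the intervention, and the 30-day claims would already capture offsetting savings within that window.
- **That a non-significant result would be taken as cost-neutral, or an increase as too expensive.** Nothing in the article says so.

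**Conclusion.** The point holds in this form: the abstract promises cost-effectiveness, while the stated aim and method cover cost alone, on a scale that does not directly estimate the mean dollar difference. The gap matters when cost and benefit rise together. It matters little if the MT arm is both cheaper and better.

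The inconsistency itself rests on the text and on no calculation. The roughly 4% to 7% divergence between equal geometric means and arithmetic means is illustrative. It depends on assumed log-normality and assumed log-SDs of 0.70 to 0.85.

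A reader might conclude that the trial is unable to address cost-effectiveness. The article does not support that, because cost, SPPB and disposition are all to be collected per patient. The shortfall is in the stated analysis, not in the data. The change should be made, but it does not touch the primary clinical analysis.

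**What to change.** In Methods for additional analyses {20b}:

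1. Make the economic estimand the difference between arms in arithmetic mean total cost, with a bootstrap confidence interval. This is worth doing even if the aim stays at cost impact.
2. Add a joint cost-effect analysis. Resample patients with their cost and effect kept together, within the unit-by-hospital randomisation strata where these are large enough. Report incremental cost per additional discharge home and per SPPB point, or net benefit over a range of willingness to pay. State the time point of each quantity, since cost runs to 30 days after enrollment while SPPB is read at discharge or day 10.
3. If no joint analysis is intended, replace cost-effectiveness in the abstract's Background with cost impact, to match Objectives {7}.

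The cost is a short addition to the analysis text, with no new patients, visits or instruments. The drawbacks are that the intervals may be wide and that the article gives no threshold for what a home discharge or an SPPB point is worth, so results would have to be shown over a range. Fixing the effect measures in advance also avoids choosing them once results are known.

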**Methods:**

The AMBULATE study is a multicenter, single-blind, parallel control design, individual-level randomized trial. It will include patients admitted to a medical service in five hospitals in two regions of the USA. Patients over age 65 with mild functional deficits will be randomized using a block randomization scheme. Those in the intervention group will ambulate with the MT up to three times daily, guided by the Johns Hopkins Mobility Goal Calculator. The intervention will conclude at hospital discharge, or after 10 days if the hospitalization is prolonged. The primary outcome is the Short Physical Performance Battery score at discharge. Secondary outcomes are discharge disposition, length of stay, hospital-acquired complications (falls, venous thromboembolism, pressure ulcers, and hospital-acquired pneumonia), and post-hospital functional status.

**Discussion:**

While functional decline in the hospital is multifactorial, ambulation is a modifiable factor for many patients. The AMBULATE study will be the largest randomized controlled trial to test the clinical effects of dedicating a single care team member to facilitating mobility for older hospitalized patients. It will also provide a useful estimation of cost implications to help hospital administrators assess the feasibility and utility of employing MTs.

**Trial registration:**

Registered in the United States National Library of Medicine clinicaltrials.gov (# NCT05725928). February 13, 2023.

## Administrative information

Note: the numbers in curly brackets in this protocol refer to SPIRIT checklist item numbers. The order of the items has been modified to group similar items (see http://www.equator-network.org/reporting-guidelines/spirit-2013-statement-defining-standard-protocol-items-for-clinical-trials/).

Role of sponsor {5c}	NIA will monitor progress of the study and will convene the Data Safety Monitoring Board (DSMB). The PI will provide NIA with interval reports of study progress with enrollment, dropouts and safety events. If there are unexpected delays, NIA may offer advice or support. NIA will convene the DSMB and ensure it has regular meetings as determined by their charter. Data will be provided to the DSMB by the study statistician. NIA may stop the study at any point if it determines there are serious safety concerns or for evidence of futility. The study statistician will prepare an analysis for futility once 40% of the patients have reached Time 2.

## Introduction

### Background and rationale {6a}

Annually, there are approximately 12.8 million adults over the age of 65 hospitalized in the USA [1]. Hospitalization contributes to functional decline of older patients [2–6]. Inpatients spend as much as 95% of their time in bed, [7] and bed rest is associated with increased risk of complications such as falls, venous thromboembolism, skin breakdown, and hospital-acquired pneumonia [8, 9]. Such adverse events delay eventual recovery and increase costs as patients spend time in both acute and post-acute (e.g., skilled nursing and inpatient rehabilitation facility) care.

Frequent in-hospital physical therapy may contribute to improved function and discharge home, [10–12] but physical therapists primarily treat patients with significant functional impairments. They should not be the first-line clinicians for providing general mobility interventions (i.e., any activity out of bed, including ambulation) [13, 14]. Evidence is growing that general mobility interventions can be facilitated by non-therapists and may mitigate adverse events and improve patients’ functional status [9, 15–26]. The studies for this evidence base, however, are mostly observational and the effects are mixed. One randomized controlled trial has shown promise, but the effect on patients’ outcomes was assessed after hospitalization [27]. In each, interventions were facilitated by a bedside nurse or a designated mobility technician. Nurses, however, have multiple competing demands that often take precedence, [28] a problem exacerbated by the COVID-19 pandemic and resulting nationwide nursing shortage [29–31]. Additionally, fall prevention strategies—which are a necessary priority for nurses—often limit mobility out of bed [32]. Primarily for these reasons, ambulation is missed approximately 75% of the time even when it is ordered by a physician [7, 33–35].

A mobility technician (MT), a clinical team member with the sole responsibility of helping patients to regularly complete general mobility interventions, may be a viable solution to these problems. However, this is not a typical role in hospitals. A lack of empirical evidence that a MT can improve outcomes makes it challenging for hospital administrators to justify the creation of MT positions since doing so would increase costs for the hospital. There is a need for non-observational studies that examine the effect of a MT on both in-hospital and post-hospital outcomes.

## Objectives {7}

AMBULATE has three primary aims: first, to determine whether an ambulation program delivered by a MT improves patients’ mobility status at hospital discharge. As related objectives, we will examine if the intervention decreases hospital-related complications, including falls, venous thromboembolism, pressure ulcers, and hospital-acquired pneumonia; if it impacts discharge disposition (i.e., home vs. post-acute care facility); and if mobility improvement is sustained after hospital discharge. Second, we will use predictive modeling to identify which patients are more likely to benefit from this intervention. Third, we will assess the impact of the intervention on overall costs associated with the episode of care, including inpatient costs and medical costs following discharge.

## Trial design {8}

The AMBULATE study is a multicenter, single-blind, parallel control design, individual-level randomized trial. It builds from our pilot trials, which demonstrated that patients with a MT ambulated more than those receiving usual care, with a small increase in mobility status, reduction in length of stay, and an increased proportion discharging home [36, 37].

## Methods: participants, interventions, and outcomes

### Study setting {9}

The study will be conducted in five hospitals—four in the Cleveland Clinic Health System (Northeast Ohio, USA) and Baystate Medical Center (Springfield, MA, USA). Each hospital will employ 2 MTs to ensure that one is always available to provide the intervention.

### Eligibility criteria {10}

Medical (i.e., non-surgical) patients in the first 48 h of their admission will be identified by the MT, aided by an automatically generated daily report and collaboration with bedside nurses on the unit. This method increases the pragmatism of the study. Participants must meet all of these inclusion criteria upon review of the medical chart in the electronic health record:≥65 years of age.Inpatient admission status to a medical service.Complete history and physical examination on file in the electronic health record.Moderate activity impairment based upon a raw score of 16–20 on the Activity Measure for Post-Acute Care (AM-PAC) 6-Clicks basic mobility short form. The 6-Clicks tool is a valid and reliable measure of function for patients in the acute hospital [38, 39]. Scores in this range are consistent with a patient who requires only a little physical assistance to complete basic mobility tasks like getting out of bed and walking, suggesting they are safe to get out of bed with a MT, but at risk of functional decline without assisted ambulation.Insurance with traditional Medicare or Medicare Advantage. This will be required to determine post-hospitalization costs.

Exclusion criteria include:Significant language barrier that requires a translator, except at Baystate where Spanish speakers may enroll since Spanish language translators are readily available.Discharge planned within 24 h of screening.Surgical procedure planned.Diagnosed with unstable angina or other medical conditions precluding participation in exercise/ambulation.Permanent residence in a skilled nursing facility.Comfort care measures only.Active infection with SARS-CoV-2 or other pathogen requiring contact or droplet precautions.An order for bed rest that is clinically warranted due to safety concerns identified by a treating physician. Whether a bed rest order meets this criterion will be clarified by the MT with the nurse.Not previously enrolled in the study.

### Who will take informed consent? {26a}

The MT will complete the informed consent process with any patient meeting inclusion/exclusion criteria. A patient who is unable to give consent can still be included if he or she otherwise meets inclusion/exclusion criteria, and a legally authorized representative gives consent. Our study has no inclusion or exclusion criteria related to race, ethnicity, sex, or gender.

### Additional consent provisions for collection and use of participant data and biological specimens {26b}

N/A. We will not collect biological specimens in this study. The potential for secondary use of data collected in this study is explained in the initial consent.

### Interventions

#### Explanation for the choice of comparators {6b}

Nurses are generally expected to perform a daily assessment of functional mobility and engage in goal setting and safe mobilization using appropriate resources, including nurse or family resources. In reality, practices vary substantially across and within nursing units on any given day due to competing needs. The randomized controlled trial design should make it more likely that intervention and control patients participate similarly in standard-of-care mobility with nurses, therapists, or family. In addition, we anticipate that on any given hospital unit there will likely be only 1 or 2 intervention patients at a time, thus decreasing the likelihood that nursing resources would be increased to assist control patients with ambulation as an unintended consequence of our study.

